### 2.4. Statistical Design

Regarding Cohort 1, considering a pCR (ypT0N0) rate of 50% or less as non-acceptable for a subsequent NOM strategy (H0 = 50%) and hypothesizing a target pCR rate of 80% following neoadjuvant tremelimumab and durvalumab, 18 patients will be required to be able to reject the null hypothesis of unacceptable pCR rate, with one-sided α- and β-errors of 0.05 and 0.20, respectively. The study treatment will be deemed promising if at least 13 pCRs will be observed.

Regarding Cohort 2, considering as non-acceptable a 2-year clinical-pathological-molecular complete response of 50% after definitive treatment and hypothesizing a target rate of 85% following tremelimumab and durvalumab, 13 patients will be required to be able to reject the null hypothesis of unacceptable rates of long-term cure, with one-sided α- and β-errors of 0.05 and 0.20, respectively. The study treatment will be deemed promising if at least 10 clinical-pathological-molecular complete responses will be observed at 2 years in absence of salvage gastrectomy.

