**Abstract:**

In resectable gastric or gastroesophageal junction cancer (GC/GEJC), the powerful positive prognostic effect and the potential predictive value for a lack of benefit from the combination of adjuvant/peri-operative chemotherapy for the MSI-high status was demonstrated. Given the high sensitivity of MSI-high tumors for immunotherapy, exploratory trials showed that combination immunotherapy induces a high rate of complete pathological response (pCR), potentially achieving cancer cure without surgery. INFINITY is an ongoing phase II, multicentre, single-arm, multi-cohort trial investigating the activity and safety of tremelimumab and durvalumab as neoadjuvant (Cohort 1) or potentially definitive (Cohort 2) treatment for MSI-high/dMMR/EBV-negative, resectable GC/GEJC. About 310 patients will be pre-screened, to enroll a total of 31 patients, 18 and 13 in Cohort 1 and 2, at 25 Italian Centres. The primary endpoint of Cohort 1 is rate of pCR (ypT0N0) and negative ctDNA after neoadjuvant immunotherapy, of Cohort 2 is 2-year complete response rate, defined as absence of macroscopic or microscopic residual disease (locally/regionally/distantly) at radiological examinations, tissue and liquid biopsy, during non-operative management without salvage gastrectomy. The ongoing INFINITY proof-of-concept study may provide evidence on immunotherapy and the potential omission of surgery in localized/locally advanced GC/GEJC patients selected for dMMR/MSI-high status eligible for radical resection.

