### 2.3. Study Endpoints

The primary objective of the study is to assess the activity of the combination immunotherapy with tremelimumab plus durvalumab as a neoadjuvant or definitive treatment of resectable MSI-H GC/GEJC. Therefore, the primary endpoint of Cohort 1 is the rate of pCR (ypT0N0) and negative ctDNA status after neoadjuvant immunotherapy in the intention-to-treat population. The primary endpoint of Cohort 2 is the 2-year complete response rate, defined as the absence of macroscopic or microscopic residual disease (locally, regionally and distantly) at radiological examinations, tissue and liquid biopsy, in absence of salvage gastrectomy.

Secondary endpoints are, for both Cohorts, 3-year DFS, defined as time from the enrollment in the study to the occurrence of disease relapse (local and/or distant), second GC/GEJC primary, or death from any cause; 5-year OS, defined as time from the enrollment in the study to the occurrence of death; metastases-free survival, defined as time from the enrollment in the study to the first evidence of metastases or death from any cause; the safety of the neoadjuvant combination immunotherapy, defined as the incidence of AEs during the treatment and follow-up phases, assessed according to common terminology criteria for adverse events (CTCAE v5.0), and its impact on patients’ quality of life, assessed thanks to patient reported outcomes (EORTC QLQ-C30, EORTC QLQ-STO22 and EuroQol EQ-5D, during pre-operative treatment phase). Additionally, for Cohort 2 the gastrectomy-free survival, defined as time from the inclusion in the study to the occurrence of gastrectomy or death from any cause, and for patients enrolled in Cohort 1 and for those enrolled in Cohort 2 and subjected to surgery, morbidity and mortality of gastrectomy following pre-operative tremelimumab and durvalumab.

Exploratory endpoints will involve translational analyses on tissue and blood biomarkers aimed at identifying which subgroup of patients may derive the highest chance of definitive cure from immunotherapy combination of tremelimumab plus durvalumab.

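### Cohort 1 declares pCR plus negative ctDNA as its primary endpoint, but its hypotheses, sample size and success rule are written for pCR alone

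*Protocol article*

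**What the plan says.** Section 2.3 (Study Endpoints) of the protocol article states that "the primary endpoint of Cohort 1 is the rate of pCR (ypT0N0) and negative ctDNA status after neoadjuvant immunotherapy in the intention-to-treat population". The abstract agrees: "The primary endpoint of Cohort 1 is rate of pCR (ypT0N0) and negative ctDNA after neoadjuvant immunotherapy".

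Section 2.4 (Statistical Design) works with a different variable. Its null is a pCR (ypT0N0) rate of 50% or less, and its alternative is set by "hypothesizing a target pCR rate of 80% following neoadjuvant tremelimumab and durvalumab". The size follows from that pair: "18 patients will be required to be able to reject the null hypothesis of unacceptable pCR rate". The error limits given there are 5% (one-sided) for a false success and 20% for a missed one. The decision rule is "The study treatment will be deemed promising if at least 13 pCRs will be observed". ctDNA does not appear in the Cohort 1 paragraph.

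The Cohort 2 paragraph of the same section does carry the molecular component into its rule, which requires "at least 10 clinical-pathological-molecular complete responses will be observed at 2 years in absence of salvage gastrectomy".

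**The concern.** A success rule should be stated on the primary endpoint. Here the endpoint section asks for two things in the same patient and the design section counts only one. The 5% and 20% error rates in Section 2.4 therefore belong to pCR, and the declared endpoint has no null, target or cut-off of its own.

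Two things are at stake. First, the same 18 patients can be a success under Section 2.4 and a failure under Section 2.3, and nothing in the article says which count decides. Second, Section 2.4 links the 50% bar to the later non-operative strategy, and the Discussion says that Cohort 2 builds on the Cohort 1 results. Section 2.5 requires liquid biopsy as part of confirming complete response in Cohort 2. The Cohort 1 rule thus leaves out a component on which the next cohort relies.

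**Working it through.** **Inputs from Section 2.4.** n = 18, cut-off r = 13, p0 = 0.50, p1 = 0.80, one-sided α 0.05, β 0.20. **Assumption.** q = P(ctDNA-negative | pCR). The article gives no value; 0.90 to 1.00 is shown.

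**Step 1. Reproduce the plan.** With X ~ Binomial(18, p) counting pCRs:
- α = P(X ≥ 13 | 0.50) = (8568 + 3060 + 816 + 153 + 18 + 1) / 2^18 = 12616 / 262144 = 0.0481.
- Power = P(X ≥ 13 | 0.80) = 0.867.
- Smaller designs miss the target: n = 16 with cut-off 12 has power 0.798, and n = 17 with cut-off 13 has 0.758.

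So 18 and 13 are correct for pCR alone.

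**Step 2. Direction.** Every patient with pCR and negative ctDNA is a pCR, so the composite count is at most the pCR count. Counting pCRs can turn a composite failure into a success, never the reverse.

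**Step 3. Smallest case that reverses the result.** Take 13 pCRs, one of them ctDNA-positive. The rule is met. The declared endpoint has 12/18 = 67%, and P(X ≥ 12 | 18, 0.50) = (18564 + 12616) / 262144 = 0.119, so the 50% null is not rejected at 0.05.

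**Step 4. Composite counted, true pCR rate 80%.** The composite rate is 0.80 × q, and power is P(X ≥ 13 | 18, 0.80q).

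| q (assumed) | composite rate | power | pCR rule met but composite below 13 |
|---|---|---|---|
| 1.00 | 0.800 | 0.867 | 0 |
| 0.98 | 0.784 | 0.825 | 0.042 |
| 0.95 | 0.760 | 0.751 | 0.116 |
| 0.90 | 0.720 | 0.609 | 0.258 |

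Because the composite event is nested in the pCR event, the last column is 0.867 minus the power. Power equals 0.80 at a composite rate of 0.775, that is q = 0.775 / 0.80 ≈ 0.97.

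**Step 5. pCRs counted, true composite rate at its 50% null.** The pCR rate is then 0.50 / q, and the chance of success is P(X ≥ 13 | 18, 0.50/q).

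| q (assumed) | pCR rate | P(declared promising) |
|---|---|---|
| 1.00 | 0.500 | 0.048 |
| 0.98 | 0.510 | 0.057 |
| 0.95 | 0.526 | 0.075 |
| 0.90 | 0.556 | 0.117 |

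**The case against.** **Shorthand.** Section 2.4 may use pCR as a short name for the endpoint defined just before it. If so, 80% is the composite target and the design stands as it is. This is possible, but the text is against it: Section 2.4 glosses pCR as ypT0N0, a purely pathological category, and names the molecular component for Cohort 2 in the next paragraph.

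**Two rates.** The endpoint wording could mean a pCR rate and a separate ctDNA-negative rate. Steps 3 to 5 would then not apply as calculated. The rule would still ignore one of the two, so the mismatch remains.

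**Power must fall below 80%.** A reader might infer this. The figures do not support it: the design has slack (0.867 against 0.80), and power on the composite stays at or above 80% for q of about 0.97 or more. At q = 1 the definitions coincide and nothing is lost.

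**Thirteen pCRs lead directly to omitting surgery.** A reader might infer this too. Section 2.1 says otherwise: Cohort 2 opens only after the results on all Cohort 1 endpoints have been evaluated, after any amendments requested by the steering and independent data monitoring committees, and with ethics committee and medicines agency approval. Section 2.5 also requires confirmation by liquid biopsy before a patient enters non-operative management. These safeguards soften the consequence. They do not settle which endpoint Cohort 1 tests.

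**Conclusion.** The point stands as an inconsistency inside the article. The Cohort 1 rule does not test the Cohort 1 primary endpoint, and the difference can only favour a positive call. That much needs no assumption beyond reading the endpoint as both criteria met in the same patient; one discordant patient among 13 pCRs is enough to separate the two conclusions.

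The size is conditional on q, which the documents do not give. For q from 0.98 to 0.90, the chance of a false success on the composite is 0.057 to 0.117 instead of 0.048. If the composite is counted with pCR at 80%, power is 0.825 to 0.609 instead of 0.867. The effect is small if nearly every pCR is ctDNA-negative and material if one in ten is not. The arithmetic of 18 and 13 is correct for the variable that Section 2.4 names.

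**What to change.** Make one definition govern the abstract, Section 2.3 and Section 2.4. Either:

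1. **Keep the composite.** State the null, the target and the rule of at least 13 of 18 for pCR plus negative ctDNA in the intention-to-treat population, and report pCR alone beside it. If 80% is the composite target, n = 18 and the cut-off of 13 stand (α 0.048, power 0.867). If 80% is the pCR rate only, state the expected q and restate the power.
2. **Keep pCR.** Declare pCR alone primary in Section 2.3 and the abstract, and make ctDNA negativity secondary.

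Which ctDNA sample counts and how missing results are handled can be left to the full protocol or the SAP.

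Cost: wording only under option 2, or under option 1 with an 80% composite target. Liquid biopsy is already scheduled at restaging (Table 1) and at surgery (Table 2), so no new samples are needed. If 80% is the pCR rate and the sponsor wants at least 80% power on the composite, the smallest designs are 23 patients with cut-off 16 at q = 0.95 (α 0.047, power 0.834) and 30 with cut-off 20 at q = 0.90 (α 0.049, power 0.806). Otherwise the lower power should be stated openly.

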### 2.5. Study Procedures

Patients meeting the eligibility criteria undergo the pre-screening phase, in which the tumor specimens are centrally evaluated at the Co-ordinating Centre and only patients with MSI-H and dMMR status confirmed according to both IHC and multiplex PCR and EBV-negative status confirmed by SISH technique may be enrolled in the study.

In both cohorts, patients are subjected to a baseline complete staging as per standard practice with chest-abdomen-pelvis CT with contrast and 18-FDG PET, endoscopic ultrasonography (EUS) as per national and international guidelines, diagnostic laparoscopy, if clinically indicated as per judgment of the Investigators and as per national and international guidelines [8,9], with the addition of liquid biopsy for detecting specific mutations, amplifications or translocations in circulating tumor DNA (ctDNA) and plasma/PMBCs collection for exploratory analyses. Subsequently, patients receive the ICIs combination for a 12-week period, tremelimumab 300 mg in single administration (day 1) and durvalumab 1500 mg every 4 weeks for 3 cycles (day 1, day 29, day 57). Between weeks 12 and 14, patients undergo a complete disease restaging, with chest-abdomen-pelvis CT with contrast, 18-FDG PET/CT, EUS with multiple random biopsies of the tumor site and fine needle aspiration biopsy (FNA) of clinically suspicious regional nodes and liquid biopsy.

In Cohort 1, all patients undergo standard gastrectomy with D2 lymphadenectomy between weeks 15 and 18 from enrollment (at least six weeks after the last treatment administration). Afterward, patients undergo a phase of follow-up with visits every 12 weeks according to the standard clinical practice and local guidelines, during the first two years or until death or disease recurrence. After the first two years, in absence of disease local or distant recurrence, patients terminate the phase of protocol-scheduled follow-up and are monitored every 6 months until the fifth year from surgery according to the standard clinical practice and local guidelines. In Cohort 2, patients who do not achieve clinical response undergo standard surgery, as in Cohort 1, while in presence of complete response confirmed by imaging/EUS, pathology and liquid biopsy, patients are subjected to a NOM and start a protocol-scheduled follow-up phase with follow-up visits repeated every 12 weeks for two consecutive years. During each follow-up visit patients undergo chest-abdomen-pelvis CT with contrast, 18-FDG PET/TC, if clinically indicated by the judgment of the investigator and not mandatory, EUS with multiple random biopsies of the tumor site and FNA of clinically suspicious regional nodes, liquid biopsy for the assessment of the presence of minimal residual disease in ctDNA. A study monitoring committee including three independent multidisciplinary teams established at the participating institutions will review the clinical records of each follow-up visit by means of an interactive video-conference system and will make decisions on the management of individual patients. At any time during the follow-up, in case of clinical suspicion or confirmation of residual GC, either at the imaging, pathologically at tissue biopsies/cytological specimens or at ctDNA in liquid biopsy, patients undergo standard surgery according to the clinical practice at their Centre. After the first two years of follow-up, in absence of disease local or distant recurrence, patients terminate the active follow-up phase and are monitored every 6 months until the fifth year according to the standard clinical practice and local guidelines. Further details are provided in Table 1, Table 2 and Table 3.

## 3. Discussion

The treatment decision-making for resectable GC/GEJC is currently based upon the clinical and pathological staging, in absence of validated biomarkers potentially able to select patients eligible for the combination with adjuvant/peri-operative chemotherapy or surgery alone [19].

The dMMR/MSI-H status is a well-established prognostic factor for prolonged survival in stage II-III CRC patients, and a potential predictive marker for the lack of benefit from adjuvant fluoropyrimidine monotherapy in stage II disease. Therefore, the indication to test for MMR/MSI status in all patients operated for stage II-III colon cancer and to consider this biomarker during the clinical management is widely accepted and recommended by all the major guidelines [10,11]. Moving to the setting of curatively resected GC/GEJC, the results of two post-hoc analyses of pivotal randomized clinical trials, MAGIC and CLASSIC studies, suggested a similar relationship between MSI-H status and patients outcomes, even though with limited statistical power due to the low prevalence of MSI-H in GC (8–10% of resectable GC patients enrolled in clinical trials) [20,21]. Afterward, an Individual Patient Data pooled analysis combining the results of four large international randomized trials in resectable GC (MAGIC, CLASSIC, ARTIST and ITACA-S) was performed, in order to evaluate the interaction between MSI status and the outcome of patients in a well-powered meta-analysis. The results confirmed the powerful positive prognostic effect of MSI-H status in surgically resected GC patients and the lack of benefit of peri-operative or adjuvant chemotherapy after surgery in this molecularly-selected subgroup [12].

Nowadays, immunotherapy revolutionized the therapeutic algorithm and provided unprecedented improvements in patients’ outcomes in several tumors, so that it now represents the standard of care in a large number of cancer types such as melanoma, non-small cell lung cancer (NSCLC) and kidney cancer. Considering GC and GEJC, the clinical trials conducted in an unselected population provided globally unsatisfactory results, highlighting the need for a molecular selection of patients according to predictive biomarkers of response to immunotherapy [22,23,24,25]. In fact, the phase III, randomized, open-label KEYNOTE-061 study, investigating pembrolizumab versus paclitaxel as second-line treatment in advanced GC or GEJC progressing after platinum and fluoropyrimidine, did not meet its primary endpoint of improving OS in the overall population, even though pembrolizumab showed a better safety profile [24]. Consistently, the KEYNOTE-062 trial compared a first-line treatment with pembrolizumab alone or combined with chemotherapy to the standard chemotherapy in advanced HER2 negative GC or GEJC, selected for PD-L1 Combined Positive Score (CPS) ≥1 and ≥10. In the CPS ≥1 population, pembrolizumab monotherapy resulted to be non-inferior to chemotherapy in terms of OS, while pembrolizumab plus chemotherapy did not demonstrate superior OS and progression-free survival (PFS) as compared to standard chemotherapy [25].

The importance of dMMR/MSI-H status emerged since these tumors, across different primary sites of origin, proved to be highly responsive to immunotherapy, to the extent that Food and Drug Administration granted an accelerated approval to the anti PD-1 antibody pembrolizumab for adult and pediatric patients with agnostic unresectable/metastatic dMMR or MSI-H cancers [13]. This was based on the analysis of the outcome of 149 selected patients enrolled in 5 clinical trials (KEYNOTE-016, 164, 012, 028, 158), among which 5 were affected by GC or GEJC. The key finding was that the objective response rate to pembrolizumab was 62% and 60% in dMMR CRC and non-CRC cancers, respectively, as compared to 0% in MMR proficient (pMMR) CRCs [13,26]. Afterward, the clinical trials introducing ICIs in the first-line treatment for dMMR/MSI-H mCRCs showed unprecedented results, setting immunotherapy as a new standard of care in this selected population. In details, in the Checkmate 142 trial, the combination of nivolumab (3 mg/kg every 2 weeks) plus low-dose ipilimumab (1 mg/kg every 6 weeks), both given until disease progression or unacceptable toxicity, reached a 64% and 58% overall response rate (ORR) and 84% and 78% disease control rate (DCR) per investigator assessment and blinded central review, respectively. Moreover, median PFS and OS were not reached at the 19.9 months median follow up, with impressive 15-month PFS and OS rates of 75% and 84% [27]. Consistently, the phase III, randomized, open-label KEYNOTE-177 trial demonstrated the superiority of pembrolizumab as compared to standard chemotherapy in terms of PFS (median PFS 16.5 vs. 8.2 months, *p* = 0.0002) with a reduced toxicity burden [28]. Considering GC or GEJC, the exploratory analyses of the KEYNOTE-059 and -061 and -062 trials showed that patients with MSI-H GC had a dramatic benefit in terms of response and survival outcomes from immunotherapy. In particular, in Cohort 1 of KEYNOTE-059, where the ORR with pembrolizumab monotherapy was 11.6% in the overall trial population, an objective response was observed in 57.1% MSI-H patients versus 9.0% of MSS ones [23]. In the KEYNOTE-061 study, patients with MSI-H tumors, irrespectively of PD-L1 CPS, had a median OS not reached with pembrolizumab versus 8.1 months with paclitaxel, and 7/15 patients (47%) achieved an objective response with pembrolizumab versus 2/12 (17%) with paclitaxel [24]. Finally, in the KEYNOTE-062 trial, in the MSI-H subgroup median OS was not reached versus 8.5 months, median PFS was 11.2 versus 6.6 months, and ORR was 57.1% versus 36.8% with pembrolizumab versus standard chemotherapy, respectively [25]. These data, together with the global burden of evidence collected so far, highlight how immunotherapy-based combinations could represent a novel standard of care for patients with MSI-H metastatic GC [14].

Moving forward, although MSI-H tumors account for about 10% of locally advanced GCs, and they display a poor or absent benefit from chemotherapy while being endowed with intrinsic sensitivity to immunotherapy, the conduction of dedicated trials with immunotherapy in the setting of MSI-H GC may be of paramount clinical relevance for a high number of cancer patients. For what concerns the use of ICIs as a neoadjuvant treatment, recent studies showed that pre-operative immunotherapy could achieve a high rate of pathologic major or complete response in potentially resectable neoplasms and eventually provide a chance to cure the tumor regardless of surgery. In fact, the priming of robust anti-tumor T cell responses necessitates the presence of an intact tumor mass [29], which provides abundant neoantigens essential for the interactions between tumor cells and immune cells [30,31]. This necessity is evidenced by the inability of ICIs to establish protective immunity after radical operations [32]. Furthermore, neoadjuvant immunotherapy results in an early establishment of immunologic memory which is absent in the adjuvant setting, contributing to the elimination of micro-metastases that otherwise may cause relapse [33]. First of all, in NSCLC, a well-known immunotherapy-responsive tumor, Forde et al. showed that two doses of the anti-PD-1 nivolumab (3 mg/kg every two weeks) in untreated, resectable (stage I-IIIA) tumors was safe and did not delay the planned surgery, while conferring a major pathological response in 9 out of 20 patients operated irrespectively of PD-L1 status, although the pre-treatment tumor mutational burden was predictive of pathologic response [34]. Afterward, Chalabi et al. [15] in the phase II NICHE study tested the combination of ipilimumab (1 mg/kg on day 1) and nivolumab (3 mg/kg on days 1 and 15) for 1 cycle as a “window of opportunity” treatment in two parallel cohorts of dMMR or pMMR resectable colon cancers. While no meaningful pathological response was reported in the 20 patients with MSS cancers, significant activity was shown in terms of disease eradication in the 20 patients with MSI-H tumors, of whom 81% had clinical stage III disease, where pCR was confirmed in 12/19 (63%) cases while all but one of the remaining cases showed a major pathological response [15]. More recently, Zhang et al. [18] reported a case series of six patients with resectable, locally advanced (cT4N+) and MSI-H gastric (*n* = 4) or colon (*n* = 2) cancers treated with anti-PD1-based regimens, even immediately after a rapid progression to standard chemotherapy. After radical surgery, 5 out of 6 patients (87%) achieved a pCR, whereas the single patient with pathological downstaging in absence of pCR had a heterogeneous mixed dMMR-pMMR cancer (a scenario previously reported in 8% of cases by Kim et al. [17]). Finally, Ludford et al. [16] published the results of a retrospective series of patients with stage IV metastatic MSI-H CRC, showing pCR in 13 out of 14 resected metastases and even after a short-duration therapy. This study highlights that immunotherapy, particularly anti-PD1 plus anti-CTLA4 combination, may provide cure even for patients with metastatic disease, consistently with the plateau of PFS curves in clinical trials with dual checkpoint inhibition (2-year PFS of about 70%) [35].

On the basis of the evidence collected, as furtherly illustrated in Table 4, and on the strong biological and clinical rationale above-discussed, the INFINITY study was designed, to evaluate the activity and safety of combination immunotherapy as a neoadjuvant or potentially definitive treatment for resectable GC/GEJC selected for MSI-H and dMMR.

The study treatment regimen consists of an anti-CTLA4 agent (tremelimumab) and an anti-PD-L1 agent (durvalumab) since the mechanisms of action of CTLA4 and PD-1/PD-L1 checkpoints are non-redundant, thus targeting both PD-1/PD-L1 and CTLA4 pathways may have an additive or even synergistic activity [36]. In fact, the combination of durvalumab plus tremelimumab proved to be safe and effective in different tumor settings such as NSCLC, head and neck tumors and recently CRC, since it demonstrated to prolong survival with manageable tolerability and preserved quality of life in metastatic CRC patients unselected for MMR status [37]. The treatment schedule of a single priming dose of tremelimumab (300 mg flat dose) combined with three doses of durvalumab (1500 mg flat dose q 4 weeks) was selected since the recently-presented D4190C00022 study showed that this schedule is endowed with the best benefit-to-risk profile and increases the proliferative CD8-positive T cells, potentially associated with tumor response [38]. This result was in line with the proven dose-dependent benefit for CTLA4 inhibitors in combination with anti-PD1/PD-L1 and with the evidence that an initial dose-dependent burst of CD4-positive T cells can be mobilized to peripheral blood after the first anti-CTLA4 agent infusion, not recurring with repeated dosing [39,40].

The single-arm multi-cohort trial design is justified considering that, given the excellent 5-year DFS (70%) and OS (75%) of patients with radically resected MSI-H GC, clinical trials comparing a neoadjuvant/peri-operative immunotherapy approach with standard of care multimodality strategy (surgery +/− neoadjuvant chemotherapy) would require a very high number of patients to be enrolled to demonstrate a significant increase of survival above the outcomes historically achieved by surgical resection. The feasibility of such a trial is even impaired by the relatively low prevalence of MSI-H status in GC (about 9% in the recent meta-analysis [12]). Finally, even when hypothesizing positive and practice-changing results of such a trial, the majority of patients eligible for peri-operative immunotherapy would be overtreated since they are most likely cured with surgery alone. Therefore, given the significant morbidity and mortality of gastrectomy, and its potentially negative impact on long-term outcomes in terms of quality of life, there is a strong rationale for investigating PD-(L)1 plus CTLA4 blockade as a definitive treatment and NOM strategy in MSI-H GC in Cohort 2 based on the results of Cohort 1 of the INFINITY Study.

